### Recruitment {15}

Several strategies will be used to achieve adequate participant enrollment as well as completeness of data acquisition. Firstly, collaborating centers are encouraged to include eligible patients by informing them by an initiation visit, regular investigator meetings, a trial website, posters, a patient animation video and an information pocket card. Secondly, potential participants are encouraged to participate by providing them with comprehensible information in multiple ways: during the hospital visits, via a patient animation video, patient information letter and a short hand-out with images. This comprehensible information is crafted in collaboration with representatives of the “brain tumor contact group” of patient organization “Hersenletsel.nl.”

## Assignment of interventions: allocation

### Sequence generation {16a}

The computer-based randomization tool Ldot ® (by MEMIC, Maastricht University, https://www.ldot.nl/) will be used. Block randomization will be done with stratification by treatment center.

### Concealment mechanism {16b}

The computer-based randomization tool Ldot will be used, which will ensure study arm allocation is not known in advance by the researcher or treating physician.

### Implementation {16c}

Authorized researchers will enroll participants. The computer-based system Ldot will generate the allocation sequence and will assign participants to the interventions. The result of Ldot will be communicated to the participant by the authorized researcher.

## Assignment of interventions: blinding

### Who will be blinded {17a}

Due to the study design in which an additional [^18^F]FET PET scan will be performed, blinding is not possible.

### Procedure for unblinding if needed {17b}

Not applicable, the patients and researchers/physicians in this trial are not blinded.

## Data collection and management

### Plans for assessment and collection of outcomes {18a}

The data will prospectively be collected from medical charts, pathology reports, radiology reports, and web-based- and hardcopy questionnaires (EORTC-QLQ-C30 + BN20, EQ-5D, iPCQ, and iMCQ). Training of assessors of the different centers is performed by meetings. The EORTC-QLQ-C30 is a 30-item questionnaire designed to measure quality of life in all cancer patients [21]. The EORTC-QLQ-BN20 was developed as a site-specific supplement to the QLQ-C30 for use among brain cancer patients. The QLQ-BN20 consists of 20 questions translated into four summary scores and seven symptom scales [22, 23].

Cost-effectiveness of the study arms will be determined from a societal perspective. Life years, QALYs, and costs will be assessed. Life years and QALYs will be informed by the trial population and EQ-5D questionnaire. The EQ-5D is a 5-item scale consisting of mobility, self-care, usual activities, pain, and anxiety [24]. The EQ-5D is a generic utility questionnaire which is used in cost-effectiveness analyses to inform health technology assessment and allows for direct comparison between different diseases [25, 26]. Costs related to healthcare services by healthcare professionals (e.g., in- and out-patient visits), diagnostics (e.g., MRI scans, blood tests), and treatments (e.g., chemotherapy) will be extracted from electronic healthcare records from participating centers. The questionnaire iMCQ will be used to reveal the type and number of consultations by healthcare professionals in the primary, secondary, and domestic care [27]. Work-related costs, such as productivity loss, will be taken into account and measured by the iPCQ questionnaire, which is applicable to national and international studies [28].

[^18^F]FET PET imaging data will be gathered from the different centers as well. To ensure reliable and comparable [^18^F]FET PET data across all participating centers, a standardized scanning and review process is implemented through multiple ways. Firstly, the PET scanners of all participating centers will be harmonized. Secondly, training of local nuclear medicine physicians will be performed. Lastly, the [^18^F]FET PET scans performed at the individual centers will undergo local analysis, but will also undergo rapid central review by a team of independent nuclear medicine physicians specialized in [^18^F]FET PET scans. This is part of clinical practice as clinical decisions are based on these [^18^F]FET PET results. In case of discordance between local analysis and central review results, a consensus meeting will be held between one/multiple centralized reviewer(s) and the local nuclear medicine physician. The result of the central review will serve as the main outcome to guide clinical management.

### Plans to promote participant retention and complete follow-up {18b}

For the outcome measure “unnecessary treatments,” no, or minimal, missing data are expected, as data are all available in the electronic patient files. Dedicated study-specific data acquisition is performed by study personnel. Due to the organization of Dutch healthcare, loss to follow-up of patients is minimal.

For the health-related quality of life questionnaires, the participants will be contacted by secured e-mails or letters and asked to complete the set of questionnaires at each time point.

When the questionnaires are not completed after a certain period, the coordinating researcher will contact the patient to explore reasons for the delay and enhance motivation and participation.

### Data management {19}

Study sites will register a patient in the secured web-based application Ldot, which will generate a unique study registration (USR) number. All data collected for the study will be stored coded in electronic case report forms in Castor EDC ® (https://www.castoredc.com/). Online and hardcopy questionnaires will be sent to the patients by Ldot.

As Ldot and Castor will be connected, data of the online questionnaires will be sent to the Castor database in a coded format, without patient identifiers. Data of the hardcopy questionnaires will be entered in the Castor database by the coordinating researcher after secured login. The hardcopy questionnaires will then physically be stored in a secure archive of the UMC Utrecht. In order to perform the central review of the [^18^F]FET PET scans for clinical decisions, [^18^F]FET PET and accompanying MRI imaging data will be shared and stored with use of the Research Imaging Architecture (RIA), a fully secure data storage infrastructure of the UMC Utrecht. All data will be analyzed by the investigators of this study and the data will be stored for a maximum of 15 years.

### Confidentiality {27}

To register a patient in Ldot, each user will get a personal account to allow secured access to his own studies, site(s), and subjects. A “role based” access to the system will avoid unauthorized data access and prevents users to perform action they are not allowed to do. After registration of the patient in Ldot, this system will generate a unique study registration (USR) number. The unique study registration (USR) number and corresponding patient identifiers (name, date of birth, sex, date of inclusion and address) will be securely stored within the Ldot database.

The participants personal data will remain confidential and will not be published in any way; however, the sponsor’s monitor or representative and regulatory representatives (FDA and/or European Communities EU Notified Body Representatives), auditors, and inspectors may have access to medical files in order to verify authenticity of data collected. Upon informed consent, patients are aware that their patient identifiers will be used in order to send questionnaires via Ldot.

### Plans for collection, laboratory evaluation, and storage of biological specimens for genetic or molecular analysis in this trial/future use {33}

Not applicable, we will not collect biological specimens as part of this study.

## Statistical methods

### Statistical methods for primary and secondary outcomes {20a}

Results will be analyzed with use of an intention-to-treat analysis.

#### Primary study parameter(s)

Unnecessary interventionsThe “unnecessary interventions” outcome will be collected as a dichotomous outcome measure (yes/no), so the percentage of patients undergoing unnecessary interventions can be calculated for both groups. Then, a two-sided *Z*-test will be performed with pooled variance with an alpha of 0.05.Health-related quality of lifeThe primary outcome HRQOL will be captured and assessed as a continuous measure by EORTC QLQ-C30 and BN20 questionnaires through a timepoint analysis at *t* = 12 weeks. Compound scores will be calculated for each patient according to the standard scoring algorithms for these questionnaires [21, 23]. Group comparisons at this *t* = 12-week timepoint will be conducted using Student’s *t* test. Results will be interpreted in terms of statistically significant difference and clinical relevance between study arms. Statistical difference will be assessed via a two-sided *p*-value ≤ 0.05.

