### Outcomes {12}

#### Primary study outcomes

##### Co-primary outcome 1

Undergoing any unnecessary intervention(s), as defined below. Determination of this dichotomous outcome measure “unnecessary interventions” will be done retrospectively, by the researchers and the treating physician after 6-month follow-up.

An “unnecessary intervention” is defined as:Biopsy or debulking for diagnostic uncertainty and/or with pseudoprogression as the final pathological diagnosis.The administration of one or more cycles of (temozolomide) chemotherapy as continued treatment for presumed pseudoprogression, in cases where the final diagnosis is tumor progression. The final diagnosis is based on clinicoradiological- and/or histopathological evidence.Starting and/or altering chemotherapy for presumed tumor progression, in cases where the final diagnosis is pseudoprogression. The administration of one or more doses of bevacizumab for presumed pseudoprogression, in cases with a final diagnosis of tumor progression.

##### Co-primary outcome 2

Health-related quality of life (HRQOL) (continuous measure): the European Organization for Research and Treatment of Cancer Quality of Life Core Questionnaire (EORTC-QLQ-C30) + Brain Cancer Module (EORTC-QLQ-BN20) at *t* = 12 weeks, preferably completed before follow-up imaging is performed.

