### Sample size {14}

From current practice (survey among the participating centers), we estimate that 37% of the glioblastoma patients that meet our inclusion criteria, eventually undergo unnecessary interventions (control arm). In the intervention arm, we expect this proportion to be much lower (~ 12% from clinical scenarios), due to the high accuracy of [^18^F]FET PET. Using a two-sided *Z* test with pooled variance with an alpha of 0.05, based on a power of 90%, we need 61 patients in each arm, so 122 in total. Due to the intention-to-treat set-up and unnecessary treatment as outcome measure, we expect that virtually all patients can be included in final analysis, with minimal drop-out. For the co-primary endpoint of HRQOL (EORTC-QLQ-C30 + BN20) at *t* = 12 weeks, drop-out due to missing questionnaire data is estimated at 10%. With addition of this drop-out rate, we will randomize 144 patients, 72 patients per study arm.

Methodologically, the two primary endpoints are hierarchical: the first (unnecessary interventions) must be met before the second (HRQOL) is formally tested. Since HRQOL may be influenced by earlier diagnosis from FET PET, the primary endpoint of unnecessary interventions should be met first to obtain a HRQOL result which is not caused solely by such a timing effect. This justifies a fixed-sequence testing approach—each tested at *p* = 0.05. If the first test is not significant, HRQOL results will be considered exploratory. The sample size was powered for the first endpoint, with a 10% increase to account for potential missing HRQOL data; a formal power calculation for HRQOL was not feasible due to limited prior data.

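### Co-primary outcome 2 names no single HRQOL score and no multiplicity rule, so step 2 of the fixed sequence is not one hypothesis and its stated 0.05 is not controlled

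*Protocol article*

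**What the plan says.** Sample size {14} makes the two primary endpoints hierarchical: "the first (unnecessary interventions) must be met before the second (HRQOL) is formally tested". It continues: "This justifies a fixed-sequence testing approach—each tested at *p* = 0.05". If the first test fails, HRQOL becomes exploratory.

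Outcomes {12} gives co-primary outcome 2 as "Health-related quality of life (HRQOL) (continuous measure): the European Organization for Research and Treatment of Cancer Quality of Life Core Questionnaire (EORTC-QLQ-C30" together with the BN20 module at 12 weeks. It names no scale or summary score.

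Statistical methods {20a}, under the primary parameters, says: "Compound scores will be calculated for each patient according to the standard scoring algorithms for these questionnaires". It then says "Group comparisons at this *t* = 12-week timepoint will be conducted using Student’s *t* test", with significance at a two-sided p-value of 0.05 or below and interpretation that also considers clinical relevance.

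Plans for assessment and collection of outcomes {18a} describes what the instruments produce. For the BN20: "The QLQ-BN20 consists of 20 questions translated into four summary scores and seven symptom scales". For the QLQ-C30 it gives the number of items but no number of scores.

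None of these sections picks one score, ranks the scores, adjusts for how many there are, or says how many must be significant for the HRQOL endpoint to be met.

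**The concern.** A fixed sequence may pass the full 0.05 to its second step only if that step is one hypothesis or a family with its own error control. Here step 2 is labelled as one endpoint but described through plural scores from two questionnaires, with nothing to reduce them to one. An HRQOL success could then be declared on whichever score crosses 0.05, and the plan would not have been breached.

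HRQOL is half of the primary objective. It is patient-reported in an unblinded trial, and it has no power calculation that would reveal which score was meant. A co-primary quality-of-life claim would lack the error control that the article states for it.

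**Working it through.** **1. The plan's own figure.** Inputs from Sample size {14}: 37% versus 12%, two-sided alpha 0.05, power 90%, pooled-variance Z test. The mean proportion is (0.37 + 0.12)/2 = 0.245.

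n per arm = [1.960·√(2·0.245·0.755) + 1.282·√(0.37·0.63 + 0.12·0.88)]² / 0.25² = (1.192 + 0.746)² / 0.0625 = 60.1, rounded up to 61. The stated 61 per arm is reproduced.

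**2. How often step 2 is reached in the planned scenario.** Power of the first test = Φ[(0.25·√n − 1.192) / √(0.37·0.63 + 0.12·0.88)].
- At n = 61: Φ(1.307) = 90.4%.
- At n = 72, the number to be randomized per arm: Φ(1.597) = 94.5%.

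Under the assumptions that the trial is built on, HRQOL is almost always formally tested.

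**3. How many scores step 2 could contain.** The article does not say. Three readings fit its words:
- k = 2: one compound score per questionnaire.
- k = 5: the four BN20 summary scores plus at least one QLQ-C30 score.
- k = 12: all BN20 scores (4 + 7 = 11) plus at least one QLQ-C30 score.

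The one score assumed for the QLQ-C30 is the minimum possible, because the article gives no count.

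**4. Chance of at least one p ≤ 0.05 at step 2 when HRQOL does not truly differ, given that the first test was passed.** For independent scores this is 1 − 0.95^k:
- 1 − 0.95² = 9.8%
- 1 − 0.95⁵ = 22.6%
- 1 − 0.95¹² = 46.0%

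For correlated scores I used equicorrelated normal test statistics with two-sided threshold 1.96. The correlations are assumptions; the documents give none.

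| Scores tested | ρ = 0 | ρ = 0.3 | ρ = 0.5 | ρ = 0.7 | ρ = 0.9 |
|---|---|---|---|---|---|
| 1 | 5% | 5% | 5% | 5% | 5% |
| 2 | 10% | 10% | 9% | 8% | 7% |
| 5 | 23% | 21% | 18% | 15% | 10% |
| 12 | 46% | 40% | 32% | 23% | 13% |

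**5. What the first test does protect.** If endpoint 1 has no true effect, any formal claim requires a false positive on it first. The overall error then stays at or below 5% whatever k is. What is lost is control when endpoint 1 truly differs and HRQOL does not.

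**6. After repair.** One named score gives k = 1 and an error of 5% at step 2. If twelve scores were all kept as confirmatory, Bonferroni would require 0.05/12 = 0.0042 for each; Holm starts at that same threshold.

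**The case against.** The strongest reply is that the article never says every scale will be tested. Outcomes {12} speaks of HRQOL as a single continuous measure. The 12-week analysis uses a t test in the singular, whereas the secondary analysis at two timepoints uses the plural; that pattern fits one test per timepoint. This stands. A reader might infer that a dozen or more unadjusted tests are planned and that the type I error is 46%, but the text supports neither. Twelve applies only if all scales are tested, and 46% further assumes that scores from the same patient on the same day are independent, which is implausible.

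It does not rescue the plan. No combined QLQ-C30 and BN20 score is described anywhere, and the scores and comparisons are plural. Even one score per questionnaire exceeds 5%. A single score chosen after the results are seen is not controlled either.

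A second reply is that the first test guards the error rate. It does so only when endpoint 1 has no true effect, which is not the scenario that the trial was designed for.

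A third is that scoring detail belongs in the full protocol or an analysis plan, neither of which is shown. A single score may indeed be named there, and nothing in the article rules that out. But the article itself states the endpoint, timepoint, test, threshold and hierarchy, and together these do not give one hypothesis. Which variable is co-primary is part of the endpoint's definition, not scoring detail.

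Finally, the sample size and the conclusion on unnecessary interventions are unaffected. That is correct and limits the reach of the point.

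**Conclusion.** The point holds as a failure to define step 2 as one hypothesis; it is not evidence that a specific number of unadjusted tests is planned. As written, the 0.05 claimed for HRQOL is not controlled when endpoint 1 truly differs.

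The size depends on a number that the article does not give. Conditional on passing the first test and on no true HRQOL effect, the false-positive chance runs from about 7–10% (two scores) through 10–23% (five) to 13–46% (twelve), for assumed equal correlations from 0.9 down to 0. The first test is passed about 94% of the time at 72 per arm if 37% versus 12% is right.

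A reader might also infer that the trial's overall error is inflated in every case. It is not: with no true effect on endpoint 1 it stays at or below 5%.

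**What to change.** In Outcomes {12}, Sample size {14} and Statistical methods {20a}, name one week-12 HRQOL score as the only confirmatory step-2 hypothesis, and make all other QLQ-C30 and BN20 scores secondary. Alternatively, list the scores that form step 2 and test them in a stated order or with Holm adjustment. If the full protocol or an analysis plan already names the score, carry it into these three sections. Settle this before any outcome data are examined by arm; recruitment is expected to run to December 2027.

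The change is wording only, with no extra patients or data. With one named score, a difference confined to another scale can no longer be claimed as co-primary. With an adjusted set, each score has less power.

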#### Other study parameters

Patient characteristics: sex, age.Oncological characteristics: date of diagnosis of initial tumor, O^6^-methylguanine DNA methyltransferase (MGMT) promotor methylation status, CDKN2A/B-status, Karnofsky performance score at baseline and during clinical examination moments.Questionnaires EORTC-QLQ-C30 + BN20, EQ-5D, iPCQ and iMCQ at baseline, measured between informed consent and randomization.Diagnostic- and treatment characteristics: surgical- and concomitant chemoradiation characteristics, usage of bevacizumab, dosage of dexamethasone, follow-up scans, blood tests.Final diagnosis during follow-up after study intervention: tumor recurrence or pseudoprogression.Notes from multidisciplinary meetings, describing diagnostic uncertainty and initial management after diagnostic imaging.

The schedule of assessments is illustrated in Table 1.

**Table 1 Tab1:** Schedule of assessments

Visit	Index MRI result	Informed consent	Randomization	FET PET^a^	FET PET result^a^				
Study time	Day 1	± Days 3–14	±Days 5–16	± Days 7–30	± Days 10–33	Week 6	Week 12	Month 6	End of trial
Unnecessary interventions								X	
EORTC-QLQ-C30 + BN20/EQ-5D/iPCQ/iMCQ		X				X	X	X	
Karnofsky performance score	X				X^a^				
Final diagnosis								X	
Survival status								X	X^b^
Healthcare consumption								X	
Adverse events^c^				X	X				

^a^The intervention group only

^b^A survival sweep will be performed at the end of the trial

^c^All possibly/probably related adverse events will be reported for 30 days in both groups. All serious adverse events will be reported for 7 days in both groups

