#### Secondary study parameter(s)

Time-to-diagnosisTime-to-diagnosis will be defined as the period from the date of the index MRI result to the date of the start of the final treatment. A Kaplan–Meier analysis will be performed. Groups will be compared with use of the log-rank test.Overall survivalOverall survival will be defined as the period from the date of the index MRI result to the date of death. A Kaplan–Meier analysis will be performed. Groups will be compared with use of the log-rank test.Number of unnecessary treatment cyclesThe number of unnecessary treatment cycles of chemotherapy and bevacizumab will be calculated for both groups. The scores of both groups will be compared by means of the Mann–Whitney *U* test. Cost-effectivenessCost-effectiveness of the study arms will be determined from a societal perspective. Life years, QALYs, and costs will be assessed (See “Plans for assessment and collection of outcomes”). Direct and indirect costs will be included in the analysis. If benefits and costs are expected to persist beyond trial time horizon, a decision analytic model will be built. If not, a trial-based economic evaluation will be conducted.The cost-effectiveness analysis will be conducted in adherence to the 2024 version of the Dutch guidelines for economic evaluations [25].Outcome of the cost-effectiveness analysis will be expressed as incremental Costs, incremental Quality-Adjusted Life Years (QALY), and Incremental Cost-Effectiveness Ratio (ICER). The results of the cost-effectiveness analysis will be combined with observed and extrapolated uptake to estimate the budget impact over time. The budget impact analysis (BIA) will be performed according to the Dutch guidelines and the BIA guideline (“BIA leidraad”) and BIA calculation tool will be utilized [29].Health-related quality of lifeThe secondary outcome HRQOL will be captured and assessed as a continuous measure by EORTC QLQ-C30 and BN20 questionnaires through timepoint analyses at *t* = 6 weeks and *t* = 6 months. Compound scores will be calculated for each patient according to the standard scoring algorithms for these questionnaires [21, 23]. Group comparisons at these timepoints will be conducted using Student’s *t* tests. Results will be interpreted in terms of statistically significant difference and clinical relevance between study arms. Statistical difference will be assessed via a two-sided *p*-value ≤ 0.05. Additionally, secondary HRQOL will be evaluated longitudinally as a continuous measure using a mixed model for repeated-measures analysis, examining changes in individual patients’ raw scores over time. Previous literature indicates HRQOL analyses become unreliable when the response rate falls below 60% of all participants [30]. Should this occur, data analysis will be limited to the timepoints that meet the 60% response criterion.PET characteristics to predict clinical outcomeIn the intervention arm, we will perform exploratory analyses of the PET characteristics, both from static and (if available) dynamic PET images, such as SUV values and SUV ratio’s, as predictors of overall survival and progression-free survival, by cox analyses.Other study parametersLastly, determinants of unnecessary interventions will be investigated, including effect modifiers of the effect of [^18^F]FET PET on outcome. In order to answer this research question, a multivariable logistic regression analysis will be performed.

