### Methods for additional analyses (e.g., subgroup analyses) {20b}

As treatment center will be used for stratification and it is expected that some of the centers will recruit small numbers of patients, no adjusting for this stratification factor will be performed in the primary analysis. However, a correction analysis for treatment center will be performed as sensitivity analysis. In addition, correction analyses for MGMT promoter methylation status (methylated versus unmethylated versus unknown), Karnofsky performance score (< 70 vs ≥ 70), and prior surgical procedure (biopsy versus resection) will be performed as sensitivity analyses [31].

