### Methods in analysis to handle protocol non-adherence and any statistical methods to handle missing data {20c}

In case more than 10% of the patients in the intervention arm do not undergo the [^18^F]FET PET scan, an additional per-protocol analysis will be performed. This traditional per-protocol analysis will be supplemented by an instrumental variable analysis in which the complier average causal effect (CACE) will be estimated for the subpopulation of patients undergoing the extra [^18^F]FET PET scan. For the primary outcome measure of unnecessary interventions, no, or minimal missing data are expected, as data are all available in the electronic patient files. Dedicated study-specific data acquisition is performed by study personnel. Due to the organization of Dutch healthcare, loss to follow-up of patients is minimal. However, in the event that missing data do occur, imputation will not be applied to the primary outcome measure; (multiple) imputation is not considered to be optimally reliable or appropriate due to the nature of this outcome and its limited predictability. The occurrence of unnecessary treatments is highly dependent on contextual factors, such as physician decision-making and the clinical course of the illness, which makes accurate imputation difficult and potentially misleading. Therefore, for this specific outcome, an available-case analysis will be conducted including only those participants with available primary outcome data—expected to be all, or virtually all randomized patients. Where appropriate, sensitivity analyses will be performed to evaluate the robustness of the findings.

Regarding the HRQOL outcomes, standards of the field will be followed by using methods that are robust to missing data, e.g., linear mixed modeling combined with single-timepoint analyses.

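### The confirmatory 12-week HRQOL test leaves the pre-randomization score and the other visits unused, and the robust method promised for missing data does not clearly reach it

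*Protocol article*

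**What the plan says.** Four places in the Protocol article bear on this point.

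- **Primary study parameter(s).** Group comparisons at the "12-week timepoint will be conducted using Student’s" t test, two-sided at 0.05. No covariate and no other visit is mentioned.
- **Other study parameters and Table 1.** The EORTC questionnaires are also completed "at baseline, measured between informed consent and randomization". Table 1 adds week 6 and month 6 to week 12.
- **Secondary study parameter(s).** After t tests at week 6 and month 6, the plan adds that "secondary HRQOL will be evaluated longitudinally as a continuous measure using a mixed model for repeated-measures analysis". The label is secondary HRQOL, and nothing links this model to the co-primary comparison.
- **Section {20c}.** The HRQOL outcomes, not limited to the secondary ones, will be handled "by using methods that are robust to missing data, e.g., linear mixed modeling combined with single-timepoint analyses".

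Two further sections set the context. Section {20b} lists adjusted sensitivity analyses for treatment center, plus "correction analyses for MGMT promoter methylation status", performance score and prior surgery. Baseline HRQOL is not on the list. Sample size {14} makes HRQOL the second formal test in a fixed sequence, at 0.05. It says that HRQOL was not formally powered and that the number randomized allows for 10% missing questionnaires.

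**The concern.** A score measured before randomization with the same instrument is usually among the best predictors of the later score. Leaving it out of the confirmatory test makes the standard error larger than it need be. That matters more here because nobody has shown that the trial has adequate power for HRQOL. If the first endpoint succeeds, HRQOL is tested formally, and a real difference could be missed for want of a covariate already in the database.

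The second issue is non-response. The t test compares those who returned a week-12 questionnaire. The trial is open-label and the arms may be managed differently, so the link between a patient's earlier condition and response at week 12 could differ by arm. The earlier scores could correct for this, but the test does not use them. Section {20c} recognizes the problem for HRQOL generally. The sections that assign methods, however, place the mixed model with the secondary outcome, so a reader cannot tell whether the confirmatory result has that protection.

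**Working it through.** **1. The plan's own figure.** There is none for HRQOL. The only sample-size figure is for unnecessary interventions: "we estimate that 37% of the glioblastoma patients that meet our inclusion criteria" have the event in the control arm, against about 12% with PET, by a pooled Z test at two-sided 0.05 and 90% power.

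n per arm = [(1.960·√(2·0.245·0.755) + 1.282·√(0.37·0.63 + 0.12·0.88)) / 0.25]² = [(1.192 + 0.746)/0.25]² ≈ 60.1, rounded up to 61.

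This reproduces the stated 61 per arm but says nothing about HRQOL.

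**2. Inputs for HRQOL.** From Sample size {14}: 72 per arm, 10% missing, so 72 × 0.9 = 64.8, taken as 65. Assumed, because the documents give no value: a true difference of 0.5 SD on one score, and a baseline-to-week-12 correlation r from 0.3 to 0.6.

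**3. Formula.** Adjusting for baseline multiplies the residual variance by 1 − r². The standardized difference becomes 0.5/√(1 − r²), and the noncentrality is that value × √(65/2). Power is from the noncentral t distribution, two-sided 0.05.

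| r | 1 − r² | Standardized difference | Noncentrality | Power |
|---|---|---|---|---|
| t test, no adjustment | 1 | 0.500 | 2.85 | 81% |
| 0.3 | 0.91 | 0.524 | 2.99 | 84% |
| 0.4 | 0.84 | 0.546 | 3.11 | 87% |
| 0.5 | 0.75 | 0.577 | 3.29 | 90% |
| 0.6 | 0.64 | 0.625 | 3.56 | 94% |

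To match the adjusted analysis, the t test needs 1/(1 − r²) times as many patients: 1.10 times at r = 0.3 and 1.33 times at r = 0.5.

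**4. Lower response.** The Secondary study parameter(s) section sets a 60% response floor for HRQOL analyses. At that floor, 72 × 0.6 ≈ 43 per arm. By the normal approximation, power for 0.5 SD is then 64% unadjusted, and 68% and 76% with adjustment at r = 0.3 and 0.5.

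**5. Non-response.** 4,000 trials per setting were simulated with 72 per arm, no true effect, and correlations of 0.4 or 0.6 between visits. The chance of a missing week-12 score depended on baseline and week-6 scores.

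| Missingness depends on earlier scores | Missing | Bias of t test | Type I error of t test |
|---|---|---|---|
| equally in both arms | about 15% to 35% | none | about 5% |
| in one arm only | about 13% | 0.08 to 0.11 SD | 7% to 10% |
| in one arm only | about 32% | 0.16 to 0.23 SD | 12% to 22% |

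In every setting, a regression on baseline and week-6 scores was unbiased, with type I error near 5%. That regression only shows that the earlier scores carry the information needed, in a setting with no week-6 treatment effect. In the proposed mixed model, week 6 would be an outcome, not a covariate.

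**The case against.** Three stronger readings are tempting, and the document supports none of them.

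- **That the t test contradicts section {20c}.** That section names single-timepoint analyses beside mixed modeling, as an example of the approach. A week-12 t test is such an analysis. What remains is narrower: the mixed-model half is attached only to secondary HRQOL.
- **That the t test is biased whenever sicker patients stop responding.** The simulation shows no bias when the mechanism is the same in both arms. The plan expects only 10% missing, excludes patients with a life expectancy under 6 months, and has non-responders contacted. Nothing in the document shows arm-specific non-response. The open-label design makes it possible, no more.
- **That chance baseline imbalance invalidates the comparison.** Randomization and the t test's standard error already allow for it. It is the precision point again, not a further one.

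There are also fair objections on size and priority. The gain depends on an unknown correlation, and at 0.3 it is only 81% to 84%. HRQOL is tested formally only if the first endpoint succeeds. The plan speaks of compound scores from two questionnaires without naming one confirmatory score, so the power figures describe a single comparison. Section {20b} gives a reason, small centers, for leaving center out of the primary analysis, and that reason stands. None of this is an argument for omitting the baseline score.

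**Conclusion.** The point holds as one of efficiency and robustness, not of an invalid test. The t test is sound with complete data or with data missing completely at random.

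The loss of precision follows from any non-zero baseline correlation. Its size rests on assumptions: at 65 per arm and 0.5 SD, between 3 and 13 percentage points of power for correlations from 0.3 to 0.6. The bias is conditional on non-response that depends on earlier scores differently in the two arms. Under that assumption, at roughly the planned level of missing data, it is about 0.1 SD.

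The wording gap is a matter of text: the confirmatory status of the mixed model is not stated, and the current labels point away from it. The change should be made, since the data are already collected and the endpoint has no power calculation to fall back on.

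**What to change.** - In Primary study parameter(s), make the formal HRQOL test the week-12 treatment contrast from the mixed model for repeated measures already planned, with week 6, week 12 and month 6 as outcomes and the baseline score as covariate. A baseline-adjusted ANCOVA at week 12 is an acceptable simpler choice. It recovers the precision but does not use week-6 scores, so it protects less against selective non-response.
- Keep the unadjusted t test as a supportive analysis.
- Keep center adjustment as the sensitivity analysis in section {20b}, and do not add it to the formal test.
- Align Primary study parameter(s), Secondary study parameter(s) and section {20c} so that all three name the same confirmatory method.

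The cost is a protocol amendment on analysis wording, reported to the ethics committee and entered in the trial registration as section {25} requires. No new data are needed. Recruitment is expected to run to December 2027, so the change can be fixed before analysis.
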